	**Time (months)**						
**Completed by patients at the GP practice or hospital**	**0**	**3**	**6**	**9**	**12**	**15**	**18**
Assessment of burden of COPD scale*	x		x		x		x
Medical Research Council*	x		x		x		x
Physical activity*	x		x		x		x
**Completed by patients at home**							
Demographics	x						x
The Saint George Respiratory Questionnaire	x		x		x		x
COPD Assessment Test	x		x		x		x
EuroQol5d-5 level Questionnaire	x		x				x
Patients Assessment Chronic Illness Care questionnaire	x				x		x
Healthcare use, medication use	x	x	x	x	x	x	x
Employment status, absence from paid work	x	x	x	x	x	x	x

*Completed by patients in the intervention group only.

#### ***Control group***

Patients in the control group will receive care as usual. The patients will visit their healthcare provider for the baseline measurement (0 months) and the 18-month follow up. At these consultations lung function and BMI will be measured, and smoking status, comorbidity, number of exacerbations in the previous year and since previous visit will be monitored. Questionnaires will be sent to patients’ homes at 0, 3, 6, 9, 12, 15 and 18 months (see Table 1).

### Outcomes

#### ***Primary outcome***

The primary outcome measure will be the proportion of patients in the intervention group with a clinically meaningful improvement on the SGRQ [19], that is, a decrease of at least 4 points between baseline and 18 month follow-up, compared with the control group.

The SGRQ consists of 50 questions with scores that range from 0 (best) to 100 (worst). Higher scores indicate more advanced impairment in health-related quality of life [12].

#### ***Secondary outcomes***

1. The net proportion of patients in the intervention group with a clinically meaningful change of 4 points on the SGRQ between baseline and 18 month follow-up [19], compared with the control group. The net proportion will be calculated by subtracting the percentage of patients improved by 4 points on the SGRQ from the percentage of patients decreased by 4 points.

2. The difference in the proportion of patients from the intervention group and control group with a clinically meaningful improvement of at least 4 points on the SGRQ (a decrease in the SGRQ score), between baseline and 6 months and between baseline and 12 months follow-up.

3. The absolute difference SGRQ score at 18-month follow-up between the intervention group and control group.

4. Health related quality of life will also be measured by the COPD Assessment Test (CAT) [20]. Differences on total scores will be calculated between baseline and 12 months follow-up and between baseline and 18 months follow-up. The CAT is an eight item questionnaire with scores ranging from 0 to 40, with higher scores indicating greater impairment of health related quality of life [20].

Differences in number of exacerbations and lung function, as recorded by the healthcare providers, will be calculated between the two groups, with respect to the number of exacerbations at a given time point and to change over time.

5. An economic evaluation will be performed at 6 and 12 months. This evaluation will compare differences in costs with differences in effects (Cost Effectiveness Analysis) and quality adjusted life years (Cost Utility Analysis).

Questionnaires will be used to record visits to physicians and healthcare providers, medication use, hospital admissions, employment status and absence from paid work every three months. For the economic evaluation, costs will be calculated from a healthcare perspective and a societal perspective.

The EuroQol5d-5 level Questionnaire (EQ-5d-5 L) measures the generic health-related quality of life. The EQ-5D-5 L consists of 5 dimensions to describe health - mobility, self-care, every day activities, pain/discomfort and anxiety/depression - each with five levels of functioning (e.g. no problems, slight problems, moderate problems, severe problems, unable to/severe problems) [21]. The domain descriptions are combined with population-based values to derive a health utility index [22]. In addition to the descriptive system and the off-the-shelf value sets, the EQ-5D-5 L includes a visual analogue scale (VAS) that individuals can use to rate their own health on a scale from 0 (worst imaginable health) to 100 (best imaginable health).

6. The process evaluation will consist of two parts: patients’ evaluation of the level of integrated healthcare will be measured at baseline, 12 months and the final visit (18 months), using the Patients Assessment Chronic Illness Care questionnaire (PACIC) [23]. The PACIC is a 20 item questionnaire, with a five point response scale (ranging from 1 = ‘almost never’ to 5 = ‘almost always’). Higher scores represent a more frequent presence of the aspect of structured chronic care. Furthermore, treatment plans (recorded in the ABC tool) will be compared qualitatively with the delivered care to patients (as reported by the patients).

A process evaluation among healthcare providers includes assessing factors that may have hindered or facilitated the implementation of the ABC tool in the management of COPD care. This evaluation, among approximately 10 to 15 participating healthcare providers, will be performed by means of semi-structured group interviews and individual interviews. Questions that will be discussed include; “How easy is it to use the ABC-tool?”, “How did patients react on the visual display?”, and “What barriers did you encounter when using the ABC scale and the ABC tool?”. The methods for the process evaluation will be described elsewhere in more detail.

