### Statistical analysis

All baseline variables and outcomes will be summarized with descriptive tables and, in the case of repeated measures, plotted against time per treatment arm.

The primary and first two secondary outcomes are binary outcomes and will be analysed with mixed logistic regression, using PQL2 or numerical integration as method of estimation.

All quantitative outcomes will be analysed with mixed linear regression, with physician, patient and measurement as three levels at which sampling error occurs, and as predictors treatment arm, time point of measurement, treatment by time interaction, patient demographics and other prognostic variables. Generalized linear mixed models with negative binomial distribution will be used to estimate the adjusted difference in exacerbations. Costs will also be analysed with generalized linear mixed models using a log-normal distribution or gamma distribution. A p-value of < .05 will be considered statistically significant.

All data will be analysed according to the intention-to-treat principle, including all randomised healthcare providers and patients. To prevent missing data, patients will receive reminders for the questionnaires if they do not return the questionnaire within three weeks. If necessary, multiple imputation to cope with missing values will be used [31].

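### Secondary outcome 1 (the net proportion on the SGRQ) is not binary, so the single mixed logistic regression assigned to it does not estimate it, and its definition uses the word 'decreased' ambiguously

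*Protocol article*

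**What the plan says.** The protocol article, under Secondary outcomes, item 1, describes a net proportion of patients with a clinically meaningful 4-point SGRQ change from baseline to 18 months, compared between arms. It is to be computed by "subtracting the percentage of patients improved by 4 points on the SGRQ from the percentage of patients decreased by 4 points".

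The Primary outcome section fixes the direction of the scale. Improvement there is "a decrease of at least 4 points between baseline and 18 month follow-up", and "Higher scores indicate more advanced impairment in health-related quality of life". Item 2 of the secondary outcomes repeats this direction: "clinically meaningful improvement of at least 4 points on the SGRQ (a decrease in the SGRQ score".

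The Statistical analysis section then states: "The primary and first two secondary outcomes are binary outcomes and will be analysed with mixed logistic regression". The first of those two secondary outcomes is the net proportion.

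**The concern.** There are two faults, and they are separate.

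- **Outcome type and model.** A net proportion needs three patient states. A logistic model takes a 0/1 event and estimates its log odds. It has no place for a patient who counts as minus one, and it cannot return a negative arm-level value. Correcting the wording of item 1 would not remove this fault.
- **Direction.** Item 1 contrasts *improved* with *decreased*, but everywhere else on this scale the article treats a decrease as an improvement. The reader has to guess that deterioration is meant, and no sign convention is given for the result.

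At stake is what gets reported for the first-listed secondary outcome. If an analyst follows the binary label, some recoding has to be invented, possibly after the data are seen. Different recodings answer different questions.

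**Working it through.** **Inputs.** Improvement rates of 50% (intervention) and 30% (control) come from the article's Sample size calculation. Worsening rates are not given anywhere in the document. I assume three pairs: 10%/30%, 20%/30% and 30%/30%.

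**The plan's own figures.** None is stated for the net proportion. The figures for the primary outcome reproduce. With unpooled variance, n per arm = (1.960 + 0.842)² × (0.25 + 0.21) / 0.04 = 90.3, against the stated 90. The inflation is 1.38 × 1.33 × 1.10 = 2.019, and 180 × 2.019 = 363, against the stated 360. These figures concern the primary outcome only.

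**Step 1: what the formula gives.** Let *I* be the percentage improved and *W* the percentage worsened. If *decreased* means deteriorated, the written formula is *W* − *I*. With worsening of 20%/30%:

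- Intervention: 20 − 50 = −30. Control: 30 − 30 = 0. Arm contrast: −30 points.
- With the order reversed (*I* − *W*): +30 and 0. Arm contrast: +30 points.

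The size is the same and only the sign differs. The standard error and two-sided p-value are therefore also the same.

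**Step 2: what kind of quantity it is.** Score each patient S = +1 (improved), 0 (unchanged) or −1 (worsened). Then the mean of S is *I* − *W*, which lies between −1 and +1. It is not the probability of a single event, and that probability is all one logistic model can estimate.

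**Step 3: what a forced binary version would do.** The obvious collapse is any change of at least 4 points, yes or no, with rate *I* + *W*. The arm contrasts are then:

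- net: (difference in *I*) − (difference in *W*)
- any change: (difference in *I*) + (difference in *W*)

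The two agree only when worsening is equal in both arms.

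| Assumed worsening, intervention / control | Net, intervention / control | Net contrast | Any change, intervention / control | Any-change contrast |
|---|---|---|---|---|
| 10% / 30% | 40 / 0 | 40 points | 60% / 60% | 0 points |
| 20% / 30% | 30 / 0 | 30 points | 70% / 60% | 10 points |
| 30% / 30% | 20 / 0 | 20 points | 80% / 60% | 20 points |

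The more the intervention prevents worsening, the more of the net effect the collapsed version loses.

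**Step 4: does a linear model on S suit?** Its arm coefficient is the difference in mean S, which is the net contrast. The variance of S, ignoring clustering, is *I* + *W* − (*I* − *W*)². In the intervention arm this is 0.60 − 0.16 = 0.44, 0.70 − 0.09 = 0.61 and 0.80 − 0.04 = 0.76 for the three scenarios. In the control arm it is 0.60 − 0 = 0.60 throughout. The variances can differ between arms, so robust or bootstrap standard errors are a sensible safeguard.

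**The case against.** The strongest reply is that the outcome can still be analysed with logistic regression. Improved yes/no and worsened yes/no are each binary. Two mixed logistic models could be fitted, and the predicted proportions subtracted to give the net per arm. Item 1 does describe a subtraction of two percentages. This stands as a possible route, so it would be too strong to say that the outcome cannot be analysed. However, the article does not say that this is the plan, and the standard error of the subtracted quantity would need its own method. A difference of two log odds ratios would not serve.

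A reader might also infer that the net is always zero, because decreased and improved would then be the same patients. The wording allows that literally, but it is not a plausible plan: a sentence that sets the two groups against each other to form a net figure must mean opposite directions. The defect is an ambiguous word, not an outcome defined as zero.

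Nor does the sign damage the inference. Worsened minus improved is a computable net deterioration, and the article states no convention that it breaks. What remains is that it runs opposite to the primary outcome, where a larger value is better, and so invites misreading.

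Finally, the any-change collapse is an illustration. The article does not propose it, and under equal worsening it does no harm.

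**Conclusion.** The outcome type and model stated for secondary outcome 1 are wrong as written: the outcome has three states, and the single mixed logistic regression assigned to it does not estimate the net proportion. This does not depend on how *decreased* is read. The wording fault is real but smaller, because on the plausible reading it changes only the sign.

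The size of any distortion depends on worsening rates that the document does not give. Over the assumed range, a binary any-change recoding would lose between 0 and 40 points of the net contrast (20 − 20 = 0 at one end, 40 − 0 = 40 at the other). No single figure should be quoted as the effect of the error.

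A reader might take this as a threat to the trial's main result. The document does not support that. The primary outcome is a proper 0/1 response, mixed logistic regression suits it, and the sample size rests on it alone. This is a correction to a secondary outcome, worth making but not critical.

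**What to change.** 1. In Secondary outcomes, item 1, define the net proportion as the percentage of patients with an SGRQ decrease of at least 4 points minus the percentage with an increase of at least 4 points, baseline to 18 months. State that a positive value favours the intervention. This also aligns the item with the *at least 4 points* threshold of the primary outcome.
2. In Statistical analysis, limit the sentence on binary outcomes to the primary outcome and secondary outcome 2.
3. Add a model for secondary outcome 1: a linear mixed model on the −1/0/+1 score with a provider random effect, using robust or bootstrap standard errors as needed. Its arm coefficient is the net difference. A mixed cumulative-logit model may be added as supportive only, since it gives an odds ratio and not the net difference.

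The cost is two edited sentences and one model statement. No new data are needed, because Table 1 already schedules the SGRQ at 0 and 18 months in both arms.

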## Methods/Design

### Study design

The study is a two-armed cluster RCT that compares an intervention group, using the ABC tool with a control group receiving usual care. The duration of follow-up period is 18 months. During this period there are seven measurements, including a baseline and final measurement. The flow of the study is presented in Figure 2.

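### The economic evaluation is set at 6 and 12 months, although follow-up, the primary endpoint and cost collection run to 18 months and Table 1 marks no EQ-5D-5L at month 12

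*Protocol article*

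**What the plan says.** In the protocol article, item 5 under Secondary outcomes gives the time points: "An economic evaluation will be performed at 6 and 12 months". It then describes the comparison: "This evaluation will compare differences in costs with differences in effects (Cost Effectiveness Analysis) and quality adjusted life years (Cost Utility Analysis"). The effect measure for the cost-effectiveness analysis is not named. The same item says that questionnaires will record visits to care providers, "medication use, hospital admissions, employment status and absence from paid work every three months".

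Other sections use 18 months:

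- Study design: "The duration of follow-up period is 18 months".
- Primary outcome: the proportion of patients with "a decrease of at least 4 points between baseline and 18 month follow-up, compared with the control group".
- Measurements, Control group: "Questionnaires will be sent to patients’ homes at 0, 3, 6, 9, 12, 15 and 18 months". The same schedule applies in the intervention group.
- Table 1: the row "Healthcare use, medication use" and the row on employment and work absence are marked at all seven time points. The SGRQ is marked at 0, 6, 12 and 18 months. The EQ-5D-5L has three marks which, by column position, fall at 0, 6 and 18 months.

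Item 2 under Secondary outcomes specifies the SGRQ responder comparison at earlier times, "between baseline and 6 months and between baseline and 12 months follow-up". The article mentions no 18-month economic evaluation and does not say why the evaluation ends at 12 months.

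**The concern.** The trial would report effectiveness over 18 months and value for money over at most 12. A reader could not combine the two, because they cover different periods and because a patient who responds at 12 months need not be a responder at 18. The Discussion says that implementation in routine care will be advised if results are as expected, so the two results are likely to be used together.

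The stated horizon also fits poorly with the data collection. Patients complete cost questionnaires at months 15 and 18 that no stated economic evaluation uses. The utility instrument has no measurement at the end of the planned 12-month cost-utility analysis but does have one at month 18. The schedule is laid out for an 18-month evaluation, and the sentence in item 5 is the exception.

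**Working it through.** The article gives no cost or cost-effectiveness figure, so there is no stated number to reproduce. The sample size of 360 rests on SGRQ response rates and is unaffected. The check compares the time points and then asks what can be said about size.

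**1. Time and questionnaires after month 12.** Follow-up is 18 months (Study design) and the latest economic time point is 12 months (item 5).

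- Time not covered: (18 − 12)/18 = 6/18 = 33%.
- Post-baseline cost questionnaires: months 3, 6, 9, 12, 15 and 18, six in all. Those after month 12 are months 15 and 18: 2/6 = 33%.

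**2. Share of costs after month 12.** Let r be the mean monthly cost in months 13–18 divided by that in months 1–12. The share is 6r/(12 + 6r). The values of r are assumptions.

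| r | Share of 18-month costs after month 12 |
|---|---|
| 0.5 | 3/15 = 20% |
| 0.75 | 4.5/16.5 = 27% |
| 1.0 | 6/18 = 33% |
| 1.25 | 7.5/19.5 = 38% |
| 1.5 | 9/21 = 43% |
| 2.0 | 12/24 = 50% |

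**3. Share of the between-arm difference captured by month 12.** For a difference d(t) in costs or utility, this is the integral of d from 0 to 12 divided by the integral from 0 to 18. The shapes are assumed.

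- Appears only after month 12: 0%.
- Grows linearly from 0: (½ × 12 × 12/18)/(½ × 18) = 4/9 = 44%.
- Starts at month 6, then constant: 6/12 = 50%.
- Constant from month 0: 12/18 = 67%.
- Declines linearly to zero at month 18: 1 − (6/18)² = 89%.
- Over by month 12: 100%.

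For a difference that keeps one sign, the range is 0% to 100%. The documents do not narrow it.

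**4. QALYs from the scheduled EQ-5D-5L.** Let u0, u6 and u18 be the utilities at the three marked times, with trapezoids and time in years.

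- 12 months: linear interpolation gives u12 = (u6 + u18)/2. QALY = 0.25(u0 + u6) + 0.25(u6 + u12) = 0.25u0 + 0.625u6 + 0.125u18. The result depends on a measurement taken six months after its own horizon.
- 18 months: QALY = 0.25(u0 + u6) + 0.5(u6 + u18) = 0.25u0 + 0.75u6 + 0.5u18. All three points are measured, but the last interval is 12 months long.

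**5. Reading of Table 1.** The columns were read from extracted text and should be confirmed on the typeset table. The neighbouring rows support the reading: the PACIC marks fall at 0, 12 and 18 months, which agrees with item 6 under Secondary outcomes.

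**The case against.** The best defence is that a secondary economic evaluation need not share the horizon of the primary endpoint. Other secondary outcomes also use earlier times, and a condensed article may leave economic detail to the full protocol or analysis plan. This stands in part: a 12-month horizon is not an error in itself. But the article does not leave the horizon open. It names the time points, gives no reason, and sets them against a schedule in which costs run to month 18 and utility is marked at month 18 but not at month 12.

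Several stronger conclusions that a reader might draw are not supported:

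- *A third of the costs is lost.* Only a third of the time and of the cost questionnaires is known to fall after month 12. The two are equal only if monthly costs are constant.
- *Costs are divided by an effect from another period.* Item 2 provides a 12-month SGRQ response with the same 4-point threshold, so costs and effect can be matched at month 12. The mismatch is with the primary result, not within the ratio.
- *The month-15 and month-18 data are not used at all.* The Statistical analysis section plans mixed models for costs without a 12-month limit. The article supports only the statement that no economic evaluation named in it covers those months.
- *Much of the intervention's own cost is dropped.* Table 1 schedules the ABC scale at 0, 6, 12 and 18 months, so three of the four scheduled uses fall within 12 months and the fourth coincides with the final measurement.

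**Conclusion.** The point holds as a conflict of horizon between item 5 and the rest of the article. As written, 6 of 18 months and 2 of 6 post-baseline cost questionnaires fall outside any stated economic evaluation, and the value-for-money result does not cover the period of the primary effect. The effect on the cost-effectiveness result cannot be sized from the documents: the cost share of 20% to 50% rests on assumed ratios of 0.5 to 2, and the share of the between-arm difference captured by month 12 is unrestricted. The support from Table 1 depends on the column reading of the EQ-5D-5L row. The primary analysis and the sample size are untouched. The change is still worth making, because the data for an 18-month evaluation are already scheduled.

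**What to change.** Reconcile item 5 under Secondary outcomes with Table 1. Make the 18-month horizon the main economic evaluation:

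- costs summed over months 0–18;
- SGRQ response at 18 months, named as the effect in the cost-effectiveness analysis;
- QALYs over 18 months from the EQ-5D-5L at 0, 6 and 18 months.

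Keep the 6- and 12-month evaluations as secondary. Pair the costs at each with the SGRQ response at the same time, and state that the 12-month QALY uses a utility interpolated between months 6 and 18.

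This takes a change to one item and some analysis work, with no new data collection. There are two downsides. More data are likely to be missing in months 12–18 than in the first year. The 18-month QALY also assumes a course of utility across a 12-month interval without measurement. Adding the EQ-5D-5L to the month-12 mailing would remove that gap and the interpolation in the 12-month QALY, but it would be an extra measurement and is not needed for the main change. If the sponsor prefers to keep 12 months as the main horizon, the reason should be stated and the missing month-12 utility addressed.

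### The cost-utility analysis is planned at 6 and 12 months, but the EQ-5D-5L is scheduled at 0, 6 and 18 months, so no patient has an observed month-12 utility.

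*Protocol article*

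**What the plan says.** The protocol article, Secondary outcomes, item 5, fixes the timing: "An economic evaluation will be performed at 6 and 12 months". The evaluation sets cost differences against effects and against "quality adjusted life years (Cost Utility Analysis").

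The utilities come from the EQ-5D-5L. The same section describes its five dimensions and says: "The domain descriptions are combined with population-based values to derive a health utility index". No other instrument in the article is given that role.

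Table 1 has columns for months 0, 3, 6, 9, 12, 15 and 18. In the part completed at home, the row for the "EuroQol5d-5 level Questionnaire" is marked at 0, 6 and 18 only. The SGRQ and CAT rows are marked at 0, 6, 12 and 18. The PACIC row is marked at 0, 12 and 18. The resource-use and employment rows are marked at every time point, in line with item 5, which records "medication use, hospital admissions, employment status and absence from paid work every three months".

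**The concern.** One of the two named times for the cost-utility analysis has no utility measurement, in either arm. The month-12 value closes the area under the utility curve for a 12-month QALY, so that QALY must rest on an assumption about a value nobody reported. The Statistical analysis section offers multiple imputation where necessary. A variable with no observed values at month 12 cannot be imputed from other patients' month-12 values, so an assumption about the course over time, or a prediction from other questionnaires, is needed. The article states neither.

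At stake is the credibility of the 12-month cost per QALY. A utility not collected at month 12 cannot be recovered afterwards.

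**Working it through.** **1. Is the table read correctly?** Reading each row against the seven month columns gives:

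| Row | Months marked |
|---|---|
| EQ-5D-5L | 0, 6, 18 |
| SGRQ | 0, 6, 12, 18 |
| PACIC | 0, 12, 18 |
| Healthcare and medication use | 0, 3, 6, 9, 12, 15, 18 |

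The PACIC row can be checked against the text, which says patients' evaluation of integrated care "will be measured at baseline, 12 months and the final visit (18 months), using the Patients Assessment Chronic Illness Care questionnaire". The two agree. The SGRQ row also fits the outcomes defined at 6, 12 and 18 months. The column positions are therefore reliable, and the empty month-12 cell for the EQ-5D-5L is not an extraction fault.

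**2. What a 12-month QALY needs.** Let u0, u6, u12 and u18 be the utilities at those months. The trapezoid rule over two half-year intervals gives

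QALY(0–12) = 0.5·(u0 + u6)/2 + 0.5·(u6 + u12)/2 = 0.25·u0 + 0.50·u6 + 0.25·u12.

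The value u12 has weight 0.25 year and is scheduled for no patient.

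**3. What the current schedule can give.** Linear interpolation sets u12 = (u6 + u18)/2. Substituting,

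QALY(0–12) = 0.25·u0 + (0.50 + 0.125)·u6 + 0.125·u18 = 0.25·u0 + 0.625·u6 + 0.125·u18.

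This can be computed from scheduled data. It makes a 12-month result depend on returning the month-18 questionnaire, in a trial whose sample size allows for 25% dropout, and it assumes a straight line across a 12-month gap.

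**4. Size of the error in one arm.** If the imputed u12 is wrong by e, the arm's QALY is wrong by 0.25·e. The values of e are assumptions, since the article gives no utilities:

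| Assumed e | Shift in one arm's QALY |
|---|---|
| 0.02 | 0.005 |
| 0.05 | 0.0125 |
| 0.10 | 0.025 |

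**5. Size of the error between arms.** The incremental QALY is wrong by 0.25·(e_intervention − e_control). With equal departures from linearity it is zero. With assumed departures of 0.05 and 0.02 it is 0.25 × 0.03 = 0.0075. Arms that follow different but straight courses from month 6 to month 18 produce no error.

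**6. Would an 18-month horizon cure it?** With month 12 observed,

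QALY(0–18) = 0.25·u0 + 0.50·u6 + 0.50·u12 + 0.25·u18.

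With only months 0, 6 and 18,

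QALY(0–18) = 0.25·u0 + 0.75·u6 + 0.50·u18.

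Take assumed utilities of 0.75, 0.80, 0.80 and 0.75 at months 0, 6, 12 and 18.

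- 12 months, u12 observed: 0.1875 + 0.40 + 0.20 = 0.7875. Interpolated (u12 = 0.775): 0.1875 + 0.40 + 0.19375 = 0.78125. Difference: 0.00625.
- 18 months, u12 observed: 0.1875 + 0.40 + 0.40 + 0.1875 = 1.175. From months 0, 6 and 18: 0.1875 + 0.60 + 0.375 = 1.1625. Difference: 0.0125.

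The one-arm error doubles, because month 12 carries weight 0.50 instead of 0.25.

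**The case against.** The strongest reply is that the analysis is weakened but not blocked. Month 12 is bracketed by scheduled utilities at months 6 and 18, and the SGRQ and CAT, both collected at month 12, could inform a prediction. An article may also leave the QALY calculation rule to a fuller plan. That stands as far as it goes: the absence of an interpolation rule is not the finding. The mismatch between a stated analysis time and a stated schedule remains, and no later plan can supply a month-12 utility that was not collected.

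A reader might infer that 12-month QALYs cannot be computed at all. Step 3 of the working shows otherwise.

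A reader might also infer that the interpolation error would use up much of any QALY gain. The documents give neither utilities nor an expected gain, and the 0.00625 in the illustration is an error in one arm's absolute QALY. It reaches the between-arm difference in full only if one arm has the whole departure from linearity and the other has none.

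Finally, a reader might object that the evaluation stops before the 18-month primary endpoint although costs and utilities are collected to month 18. That is a preference about horizon. A 12-month economic horizon contradicts nothing in the article.

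**Conclusion.** The inconsistency is real and narrow. The 12-month cost-utility analysis has no observed end value for the QALY in either arm. The one-arm consequence is 0.25·e, or 0.005 to 0.025 QALY for assumed errors of 0.02 to 0.10. The effect on the incremental QALY depends on how far the departure from a straight line differs between arms, and the documents give no basis for putting a figure on that. The range rests on trapezoid weighting.

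The 6-month cost-utility analysis, the 12-month costs and the SGRQ-based cost-effectiveness analysis at 12 months are supported by the schedule. The primary outcome and the sample size are untouched. The point should be fixed, but it concerns one part of one secondary outcome at one of two time points and does not threaten the trial's main result.

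**What to change.** Reconcile item 5 of the secondary outcomes with Table 1 by adding the EQ-5D-5L to the month-12 home questionnaire, so that all three terms of the 12-month QALY are observed. The cost is five items and a VAS in a mailing that already carries the SGRQ, CAT, PACIC and resource-use questions, with no extra visit. If the EQ-5D-5L is in fact already sent at month 12, correcting Table 1 is enough.

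Moving the evaluation to 6 and 18 months would make the wording consistent and give an observed end value, but it is not an equivalent cure because the utility gap between months 6 and 18 stays. If month 12 cannot be added and the 12-month horizon is kept, specify in advance how u12 will be obtained, with a sensitivity analysis on that assumption.
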